**3.4 Inclusion Criteria**

- - 6 weeks 0 days to7 weeks 6 days age at the time of enrollment.
  - Healthy infant free of chronic or serious medical condition as determined by history and physical exam at time of enrollment into in the study.
  - Written informed consent obtained from the parents or guardians.
  1. **Exclusion Criteria**
- Hypersensitivity to any of the vaccine components.
- Use of any investigational drug or vaccine other than the study vaccine within 30 days of first dose of study vaccine or during the study.
- Use of any immunosuppressive drugs.
- Previous intussusceptions or abdominal surgery.
- Enrolment in any other trial (Simplified Antibiotic Therapy for Neonatal Sepsis Trial, Management of Omphalitis Trial).
- Birth weight less than 1500 grams; or if birth weight is unknown, weight less than 2000 grams on or before 28 days.
- Immunoglobulin and/or blood products use since birth or during the study period.

Rotavirus vaccine administration should be postponed in subjects who, per the clinician’s assessment:

- - Have vomited during each of the last three feedings
  - Are recommended for hospitalization at the visit
  - Are suffering from acute febrile illness. Acute febrile illness is defined as temperature ≥ 38.0^o^ measured by rectal or axillary thermometer (Meet WHO criteria for moderate to severe dehydration (= those needing ORS rehydration in the facility or intravenous rehydration).
  - EPI vaccinations will be provided or postponed as per the clinician’s assessment and according to standard practice.
  1. **Elimination Criteria During the Study**
- Rotavirus IgA seropositivity in the blood specimen obtained at age 6 weeks, if the results become available before the time additional rotavirus vaccine doses are due to be given or additional blood draws or other samples are due to be obtained. These children will not be included in the final analysis, since they are already seropositive and cannot seroconvert due to rotavirus vaccine. If the 6-week IgA results become available before the time additional rotavirus vaccine doses are due or study samples are scheduled to be obtained, these children will not receive further rotavirus vaccine doses or undergo further blood draws or study sample collection; however, we will ensure that they continue to receive the routine EPI vaccines.
- Infants who develop intussusceptions during the study will not receive additional doses of rotavirus vaccine.

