**Study B: Impact of withholding breastfeeding around the time of Rotarix® vaccination on the immunogenicity of Rotarix® vaccine.**

- 1. **
[figure not shown]
Study Site**

The study will be conducted at one site in an urban- squatter settlement area, Ibrahim Haidry in Karachi where the Aga Khan University’s Department of Paediatrics and Child Health has demographic surveillance in place, including pregnancy and newborn surveillance. The annual birth cohort in the area is approximately 1800 infants. The site is about 30 minutes driving distance from the Aga Khan University Medical College and Hospital campus. A GIS map of the site is available. The Department will provide EPI immunizations at this location.

- 1. **Study Design**

This study will compare the immunogenicity of Rotarix ® vaccine in relation to the timing of breast feeding. The two arms of the study will receive the EPI vaccines according to the usual schedule in Pakistan at ages 6, 10 and 14 weeks and Rotarix® vaccine at 6, 10, and 14 weeks of age. In arm 1, mothers would be asked to breast feed immediately before administration of the Rotarix dose. In arm 2, mothers would be asked to withhold breast feeding for one hour before and one hour after each Rotarix®dose.

Infants potentially eligible for the study will be identified by the CHWs during their routine household surveillance, and will be brought to the PHC at 4 weeks of age or at the time of first contact with the baby. In the PHC, infants will undergo history and physical examination by the study medical officer to determine eligibility. Study procedures will be explained to the mothers, including the need to withhold breastfeeding or to breastfeed at time of the vaccine doses, depending on the study arm. Consent will be asked from the parents of infants who are eligible. After obtaining consent, infants will be randomized into the breast feeding with holding or immediate breastfeeding arms.

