Mothers who earlier provided consent and were randomized to the immediate breastfeeding group will be picked up at their home approximately 1 hour before the expected immunization time and instructed not to breastfeed until the indicated time. They will be taken to the clinic, infant blood sample will be obtained, routine EPI immunization will be given and mother will be asked to breastfeed the baby for at least 20 minutes. CHW staff will observe the breastfeeding. The Rotarix vaccine will be given, and then baby will be observed for 20 minutes to document if any vomiting occurred.

Mothers who earlier provided consent and were randomized to the withholding breastfeeding group will be picked up at their home approximately 1 hour before the expected immunization time and instructed not to breastfeed until the indicated time. They will be taken to the clinic, infant blood sample will be obtained, routine EPI immunization will be given, Rotarix vaccine will be given, and then mother will be asked to not breastfeed for one hour after the dose. CHW staff will observe the mother and infant during this period and document withholding of breastfeeding and to document if any vomiting occurred. After the 1 hour period, the mother will be able to breastfeed the infant if desired.

On the day of each vaccine visit, the mother will be asked to express 10 ml of breast milk into a study container while the CHW is present in the home to assist as needed or in the clinic and to refrigerate the sample as soon as it is expressed.

At age 6, 14 and 18 weeks, in breast feeding withholding arm 1 ml of oral fluid (OF) will be taken from infants in order to determine the correlation of IgA in OF and serum. Arm 1 provides an ideal setting to assess the value of non-invasive OF assays for rotavirus immune response, avoiding the potential contamination from breast milk.

- 1. **Sample Size consideration:**

Target enrollment would be 400 infants (200 each in each group) to be able to detect a difference in seroconversion rate of at least 17.5% between the withholding breastfeeding group and the immediate breastfeeding group, if such a difference truly exists.

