Assumptions used for calculation of sample size are an estimated seroconversion rate in the immediate breastfeeding infants of 45% at age 18 weeks and in the withholding breastfeeding infants of 62.5% at age 18 weeks; power at 0.85, and a two-sided alpha of0.05. Using a Chi-square test and assuming 20% drop out and 5% baseline IgA seropositivity at 6 week, the estimated sample size needed in each group is 191.

- 1. **Study schema**

CHWs will identify healthy infants younger than 5 weeks of age on their routine surveillance using the enrollment checklist

Parents or caretaker of eligible infants will be provided transportation for required visits to PHC

Child referred to PHC for enrollment and randomization at 5 weeks

History and physical examination by PHC Medical Officer to assess eligibility

Consent asked from parents of eligible infants

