**Visit at 18 weeks**

- Blood and oral fluid samples obtained from infant
  1. **Lab Assay**

| **Youngest (Y): 6wk, 0dy**  **Oldest(O): 7wk, 6dy** | **Y: 10wk, 0dy**  **O: 12wk, 6dy** | **Y: 14wk, 0dy**  **O: 17wk 6dy** | **Y: 18wk, 0dy**  **O: 22wk, 6dy** |
| --- | --- | --- | --- |
| ***Infant serum*** |  | ***Infant serum*** | ***Infant serum*** |
| Rotavirus IgA  Neutralizing Antibodies |  | Rotavirus IgA | Rotavirus IgA |
| ***Oral fluid(withholding group only )*** |  | ***Oral fluid(withholding group only )*** | ***Oral fluid(withholding group only )*** |
| Rotavirus IgA |  | Rotavirus IgA | Rotavirus IgA |
| ***Breast milk sample*** | ***Breast milk sample*** | ***Breast Milk sample*** |  |
| Rotavirus IgA  Rotavirus Neutralizing Activity | Rotavirus IgA  Rotavirus Neutralizing Activity | Rotavirus IgA  Rotavirus Neutralizing Activity |  |

- 1. **Sampling Collection and Handling**

Same as section 3.13

- 1. **Laboratory Training and testing for rotavirus antibody assays**

Serum rotavirus IgA and rotavirus neutralizing antibody testing will be done as described in section 3.15. Assessment of rotavirus antibody and rotavirus neutralizing activity in breast milk, and rotavirus antibody in oral fluid will be done at CDC- [name] lab, who is the pioneer of this assay.

- 1. **Data Entry, Cleaning and Management**

Same as section 3.16

- 1. **Data Analysis of Demographics**

Same as section 3.16

- 1. **Analysis of immunogenicity**

Seropositivity will be defined as an anti-rotavirus IgA concentration ≥20 U/ml. Seroconversion will be defined as the detection of anti-rotavirus IgA concentration ≥ 20 U/ml in infants seronegative for anti-RV IgA at age 6 weeks before vaccination. The primary analyses will be performed on the according to protocol (ATP) cohort. The primary endpoint will be the comparison of the rotavirus IgA seroconversion rate at age 18 weeks between the immediate breastfeeding and the withholding breastfeeding groups, using a Chi-square test. Confidence intervals (95%) for the difference in seroconversion rates will also be calculated. Rotavirus IgA GMC (geometric mean concentration) at age 18 weeks will be calculated and compared between the arms using a t-test. Similar analyses will be performed comparing the seroconversion rate at age 14 weeks between the two arms.

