The correlation between serum and OF IgA will be determined (1) by the concordance in detecting seroconversion, as defined above, at 14 and 18 weeks and (2) the correlation between antibody titers in OF and serum at age 6,14 and 18weeks. For this analysis a cutoff will not be used. Instead, the simple correlation (represented by the R-squared value) will be calculated between anti-rotavirus IgA titer in serum compared with anti-rotavirus IgA titer in oral fluid. This will give the best indication of how well oral fluid antibody represents antibody in serum.

- 1. **Role of Rotavirus Neutralizing activity in Breast Milk on the immunogenicity of Rotavirus vaccine:**

The distribution of the level of rotavirus neutralizing activity in breast milk samples (among those infants who were rotavirus IgA negative at age 6 weeks and completed the study ATP) will be examined. The independent effect of the level of breast milk neutralizing activity on the rate of rotavirus IgA seroconversion at age 18 weeks will be assessed using logistic regression. Breast milk arm (immediate vs. withholding) and level of rotavirus neutralizing antibody in 6-week serum sample will be included as independent variables and effect modification will be examined. Analyses will also be performed using rotavirus IgA seroconversion rate at age 14 weeks as the endpoint. Exploratory analyses will be performed for correlation between level of breast milk neutralizing activity (in breast milk samples at ages, 6, 10 and 14 weeks) and rotavirus IgA level at ages 14 and 18 weeks in the different two arms.

- 1. . **Enrollment Time Period**

Refer to section 5

- 1. **Inclusion Criteria :**

Same as section 3.4

AND

- Mother reports she intends to breastfeed her infant through at least age 14 weeks (Exclusive or non exclusive breast feeding).
  1. **Exclusion Criteria**

Refer to section 3.5

AND

- Biological mother not available for participation in the study.
  1. **Elimination Criteria During the Study**

Refer to section 3.6

- 1. **Contraindication of the Vaccine**

Refer to section 3.7

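### Study B gives three incompatible ages for enrolment and randomisation, and randomises before the baseline blood sample with no stated concealment in between

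*Protocol*

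**What the plan says.** All references are to the protocol.

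- **Study B, Inclusion Criteria:** "Same as section 3.4", plus the mother's intention to breastfeed to at least 14 weeks. No separate age rule is set for Study B.
- **Section 3.4 (Study A), imported by Study B:** "6 weeks 0 days to7 weeks 6 days age at the time of enrollment".
- **Study B, Study schema:** "CHWs will identify healthy infants younger than 5 weeks of age on their routine surveillance using the enrollment checklist", followed by "Child referred to PHC for enrollment and randomization at 5 weeks".
- **Study B, Study Design:** infants "will be brought to the PHC at 4 weeks of age or at the time of first contact with the baby". Eligibility and consent are handled there, and then "After obtaining consent, infants will be randomized into the breast feeding with holding or immediate breastfeeding arms".
- **Study B, Study Design, on the vaccine visits:** mothers in both arms are described as already consented and randomised. Both are collected from home about an hour beforehand and "instructed not to breastfeed until the indicated time".
- **Study B, Lab Assay table, first column:** "Youngest (Y): 6wk, 0dy Oldest(O): 7wk, 6dy". The visit flow puts the pre-vaccine blood sample and the first dose at this visit.
- **Study B, Analysis of immunogenicity:** seroconversion is defined only for infants seronegative at 6 weeks before vaccination, and the primary analysis uses the according-to-protocol (ATP) cohort.

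Study A, under Recruitment Process, approaches families at 4 to 6 weeks but obtains consent, enrols and opens the sealed envelope at 6 weeks.

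**The concern.** Two problems follow from these passages.

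**Eligibility.** The age criterion applies at enrolment, and the schema makes enrolment and randomisation one step at an age below the criterion's lower limit. A site following the schema breaks the criterion. A site following the criterion cannot follow the schema.

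**Loss before baseline.** Randomisation comes before the sample that decides whether an infant can be analysed at all. A mother told to feed, or not to feed, around each dose cannot be blinded. The Study B text describes no step that holds the allocation back until the 6-week visit. A family that withdraws in between has been randomised but contributes nothing to the seroconversion comparison. If willingness to return depends on the arm, the arms compared are no longer the arms randomised.

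**Working it through.** **1. The plan's own sample size.** This is reproduced for context and is not in dispute. Inputs from Study B, Sample Size consideration: 45% against 62.5%, two-sided alpha 0.05, power 0.85, 20% dropout, 5% seropositive at baseline.

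n = [z(0.975)·√(2·p̄·q̄) + z(0.85)·√(p₁q₁ + p₂q₂)]² / (p₂ − p₁)², with p̄ = 0.5375

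= [1.960·√0.4972 + 1.036·√0.4819]² / 0.175² = 144.2, so 145 evaluable per arm.

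145 / (0.80 × 0.95) = 190.8, so 191. This matches the stated figure.

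**2. Ages in days.** 4w0d = 28; 5w0d = 35; 5w6d = 41; 6w0d = 42; 7w6d = 55.

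**3. Shortfall against the minimum age of 42 days, and gap to the first-dose window of 42 to 55 days.**

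| Age at randomisation | Days below minimum | Days to baseline blood and first dose |
|---|---|---|
| 4w0d | 42 − 28 = 14 | 42 − 28 = 14 to 55 − 28 = 27 |
| 5w0d | 42 − 35 = 7 | 42 − 35 = 7 to 55 − 35 = 20 |
| 5w6d (5 weeks read as completed weeks) | 42 − 41 = 1 | 42 − 41 = 1 to 55 − 41 = 14 |

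No reading of the schema's 5 weeks reaches 42 days. Taking 4w0d and 5w0d, the gap is 7 to 27 days. The first-contact route fixes no age, so no shortfall or gap can be calculated for it; an infant first met at 42 to 55 days would meet the criterion.

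**4. Is early allocation needed?** In the Study B design text both arms have the same home collection, no-feeding instruction, blood draw and EPI vaccination. They part only afterwards, in the clinic, when one mother feeds before Rotarix and the other does not. The one earlier arm-specific item is the pre-vaccine oral-fluid sample, taken in the withholding arm only. It too is collected at the 6-week visit. Nothing described before that visit depends on the arm.

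**5. What loss in the gap would do to power.** The protocol gives no figure for this loss. The values below are assumptions: the loss is equal in both arms and comes on top of the planned 20% dropout. Evaluable per arm = 200 × (1 − loss) × 0.80 × 0.95.

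| Assumed loss before dose 1 | Evaluable per arm | Power |
|---|---|---|
| 0% | 152 | 86.8% |
| 5% | 144 | 85.0% |
| 10% | 137 | 83.1% |
| 20% | 122 | 78.5% |

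Modest loss costs little power. The more important issue is whether the loss is related to arm, and the documents cannot settle that.

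**The case against.** The best defence is that this is a wording conflict with limited effect. Much of it stands:

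- **Dosing and sampling.** An infant randomised early would still be sampled and dosed within 6w0d to 7w6d. The endpoint, test and sample size are untouched.
- **Arm-related loss.** Feeding procedures are explained before consent, so a mother who objects to either can decline before randomisation. Both arms also get the same instruction until the clinic. Arm-related loss is therefore a possibility, not a demonstrated effect.
- **Disclosure.** No sentence says when the mother learns her arm. That she may know it during the gap is an inference from the open nature of the arms and the absence of any stated concealment.

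Three stronger readings are tempting, and the protocol supports none of them:

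- **A reader might infer that all 400 Study B infants are outside the age criterion.** That follows only if the schema overrides the design text, whose first-contact clause could admit an infant first seen at 6 to 7 weeks.
- **A reader might infer that the ATP cohort would be empty.** The protocol names that cohort without giving its membership rules, and nothing makes age at randomisation one of them.
- **A reader might attach a specific arm imbalance to the gap.** The documents give no loss rate for this interval, in total or by arm.

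The defence does not remove the contradiction. No passage sets a different age for Study B, and the vaccine-visit text confirms that randomisation comes earlier, so this is not just loose use of the word enrolment. Changing the age criterion alone would make the text consistent but leave the gap before baseline.

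**Conclusion.** The point holds. Section 3.4, the Study B schema and the Study B design text give incompatible ages for one step of a randomised comparison, and nothing in the protocol resolves them. Infants handled under the schema fall 1 to 7 days below the stated minimum, depending on how 5 weeks is read. Those randomised at 4w0d fall 14 days below.

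Randomisation precedes baseline blood and first dose by about 7 to 27 days, or by as little as 1 day on the completed-weeks reading. In that interval the protocol describes no concealment, and a lost infant cannot enter the seroconversion analysis. The resulting loss is avoidable and may be related to arm; its size is unknown. The conclusion assumes that enrolment in section 3.4 means the same event as in the schema, and that the allocation can become known once it is made.

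**What to change.** Keep identification, explanation and consent at 4 to 5 weeks. At the 6-week clinic visit, confirm the section 3.4 criteria, take the pre-vaccine blood sample, then enrol and open the allocation envelope. Do this before the oral-fluid sample, which only the withholding arm gives, and before the arms part over feeding. Study A already enrols and opens its envelope at 6 weeks, although it does not fix the order relative to the blood draw. The Study B text describes no envelope, so it should state that the Study A method applies.

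Revise the Study B design text (the age at the clinic visit and the vaccine-visit paragraphs that treat mothers as already randomised), the Study B schema and the Study B inclusion criteria so that all agree with section 3.4. Define screening, consent, enrolment and randomisation as separate dated steps.

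The cost is protocol wording and envelope handling at the clinic, with no added visit. Staff must be ready for either arm at each first visit. Exclusions for a seropositive 6-week sample, and dropout after the first dose, remain as planned.

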**Eligible Not eligible**

Exit

Consent by study

Physician

**Consent declined**

**Consent given**

Randomized in withholding breast feed or immediate breast feeding arm

- 1. **Breastfeeding Immunogenicity Study**

**Withholding Breastfeeding Arm (Arm 2)**

n= 200

**Immediate Breastfeeding Arm (Arm 1)**

n=200

**Visit at 6 weeks**

- Breast milk sample obtained from mother
- Pre vaccine blood sample obtained from infant
- EPI vaccines given
- 1^st^ dose Rota virus vaccine
- Breast feed immediately before vaccination

**Visit at 6 weeks**

- Breast milk sample obtained from mother
- Pre vaccine blood and oral fluid samples obtained from infant
- EPI vaccines given
- 1^st^ dose Rota virus vaccine
- One hour withholding of breast feed before and after vaccination

**Visit at 10 weeks**

- Breast milk sample obtained from mother
- EPI vaccines given
- 2^st^ dose Rota virus vaccine
- One hour withholding of breast feed before and after vaccination

**Visit at 10 weeks**

- Breast milk sample obtained from mother
- EPI vaccines given
- 2^st^ dose Rota virus
- Breast feed immediately before vaccination

**Visit at 14 weeks**

- Breast milk sample obtained from mother
- 3^rd^ dose Rota virus vaccination
- Blood sample obtained from infant
- EPI vaccines given
- Breast feed immediately before vaccination

**Visit at 14 weeks**

- Breast milk sample obtained from mother
- 3^rd^ dose Rota virus vaccination
- Blood and oral fluid samples obtained from infant
- EPI vaccines given
- One hour withholding of breast feed before and after vaccination

**Visit at 18 weeks**

- Blood sample obtained from infant

**Visit at 18 weeks**

- Blood and oral fluid samples obtained from infant
  1. **Lab Assay**

| **Youngest (Y): 6wk, 0dy**  **Oldest(O): 7wk, 6dy** | **Y: 10wk, 0dy**  **O: 12wk, 6dy** | **Y: 14wk, 0dy**  **O: 17wk 6dy** | **Y: 18wk, 0dy**  **O: 22wk, 6dy** |
| --- | --- | --- | --- |
| ***Infant serum*** |  | ***Infant serum*** | ***Infant serum*** |
| Rotavirus IgA  Neutralizing Antibodies |  | Rotavirus IgA | Rotavirus IgA |
| ***Oral fluid(withholding group only )*** |  | ***Oral fluid(withholding group only )*** | ***Oral fluid(withholding group only )*** |
| Rotavirus IgA |  | Rotavirus IgA | Rotavirus IgA |
| ***Breast milk sample*** | ***Breast milk sample*** | ***Breast Milk sample*** |  |
| Rotavirus IgA  Rotavirus Neutralizing Activity | Rotavirus IgA  Rotavirus Neutralizing Activity | Rotavirus IgA  Rotavirus Neutralizing Activity |  |

- 1. **Sampling Collection and Handling**

Same as section 3.13

- 1. **Laboratory Training and testing for rotavirus antibody assays**

Serum rotavirus IgA and rotavirus neutralizing antibody testing will be done as described in section 3.15. Assessment of rotavirus antibody and rotavirus neutralizing activity in breast milk, and rotavirus antibody in oral fluid will be done at CDC- [name] lab, who is the pioneer of this assay.

- 1. **Data Entry, Cleaning and Management**

Same as section 3.16

- 1. **Data Analysis of Demographics**

Same as section 3.16

- 1. **Analysis of immunogenicity**

Seropositivity will be defined as an anti-rotavirus IgA concentration ≥20 U/ml. Seroconversion will be defined as the detection of anti-rotavirus IgA concentration ≥ 20 U/ml in infants seronegative for anti-RV IgA at age 6 weeks before vaccination. The primary analyses will be performed on the according to protocol (ATP) cohort. The primary endpoint will be the comparison of the rotavirus IgA seroconversion rate at age 18 weeks between the immediate breastfeeding and the withholding breastfeeding groups, using a Chi-square test. Confidence intervals (95%) for the difference in seroconversion rates will also be calculated. Rotavirus IgA GMC (geometric mean concentration) at age 18 weeks will be calculated and compared between the arms using a t-test. Similar analyses will be performed comparing the seroconversion rate at age 14 weeks between the two arms.

The correlation between serum and OF IgA will be determined (1) by the concordance in detecting seroconversion, as defined above, at 14 and 18 weeks and (2) the correlation between antibody titers in OF and serum at age 6,14 and 18weeks. For this analysis a cutoff will not be used. Instead, the simple correlation (represented by the R-squared value) will be calculated between anti-rotavirus IgA titer in serum compared with anti-rotavirus IgA titer in oral fluid. This will give the best indication of how well oral fluid antibody represents antibody in serum.

- 1. **Role of Rotavirus Neutralizing activity in Breast Milk on the immunogenicity of Rotavirus vaccine:**

The distribution of the level of rotavirus neutralizing activity in breast milk samples (among those infants who were rotavirus IgA negative at age 6 weeks and completed the study ATP) will be examined. The independent effect of the level of breast milk neutralizing activity on the rate of rotavirus IgA seroconversion at age 18 weeks will be assessed using logistic regression. Breast milk arm (immediate vs. withholding) and level of rotavirus neutralizing antibody in 6-week serum sample will be included as independent variables and effect modification will be examined. Analyses will also be performed using rotavirus IgA seroconversion rate at age 14 weeks as the endpoint. Exploratory analyses will be performed for correlation between level of breast milk neutralizing activity (in breast milk samples at ages, 6, 10 and 14 weeks) and rotavirus IgA level at ages 14 and 18 weeks in the different two arms.

- 1. . **Enrollment Time Period**

Refer to section 5

- 1. **Inclusion Criteria :**

Same as section 3.4

AND

- Mother reports she intends to breastfeed her infant through at least age 14 weeks (Exclusive or non exclusive breast feeding).
  1. **Exclusion Criteria**

Refer to section 3.5

AND

- Biological mother not available for participation in the study.
  1. **Elimination Criteria During the Study**

Refer to section 3.6

- 1. **Contraindication of the Vaccine**

Refer to section 3.7

